### Outcome measures

The primary clinical effectiveness measure is the difference in BMI z-scores between the two study arms at 12 month follow-up. The primary outcome for the economic evaluation is the incremental cost per Quality Adjusted Life Year (QALY). The primary analysis is a cost-utility analysis however additional cost-effectiveness analysis using outcomes such as cost per unit of BMI z-score change or wellbeing will be conducted. Secondary outcomes include BMI z-score at 4 months, change in wellbeing, academic attainment, physical fitness and staff wellbeing (described in more detail under the data collection section below).

### Data collection

#### Clinical measurements

Participant’s height and weight are measured in school at baseline, 4 and 12 months, by trained researchers using a standard protocol. Measurements are taken without shoes on and while wearing light clothing. The Leicester Height Measure is used to measure standing height to the nearest millimetre. Height is measured twice, with a third observation taken if the values differ by greater than 4 mm. Weight (to the nearest 0.1 kg) and body fat percentage are measured using a Tanita bioimpedance monitor (Tanita SC-331S; Tanita Corporation., Tokyo, Japan). BMI z-scores are calculated using LMSgrowth software [14] which uses age and gender specific British 1990 growth data [15] to convert height and weight data to standard deviation scores using the LMS method [16].

Physical fitness is measured in school by school staff using the British Athletics Linear Track Test. Participants are encouraged to run as far as they can in two minutes on a pre-measured 50 m linear track. The distance achieved is recorded to the nearest 5 m and provides their endurance score.

#### Quality of life and wellbeing measures

Two quality of life/wellbeing questionnaires (Child Health Utility 9 Dimension (CHU 9D) and Middle Year Development Instrument (MDI)) are completed by the participants electronically in the classroom with teacher supervision. The CHU 9D is a generic health-related quality of life (HRQL) measure for children aged between 7 and 11 [17]. It is a self-report questionnaire requiring children to respond based on how they are feeling ‘today’. The questions address worry, sadness, pain, tiredness, annoyance, problems with school work, their daily routine and their ability to join in with activities. The CHU 9D was developed with the intention of being used as a preference based measure for use in paediatric economic evaluations. The MDI measures children’s social and emotional health and well-being in middle childhood (ages 6–12) [18]. This is a time when children experience important changes that establish their identity and impact their adolescent and adult development. The MDI is a self-report, multiple choice questionnaire asking children about their thoughts, feelings and experiences. Two index scores are produced: MDI Well-being Index and MDI Assets Index. Assets are quantities present in children’s lives that make a difference.

All class teachers are asked to complete a measure of wellbeing, the Warwick-Edinburgh Mental Well-being Scale (WEMWBS) [19]. This is a 14-item self-report questionnaire designed to measure mental wellbeing in adults and young people (aged 16 and above) over the last 2 weeks. It was developed in the UK and has been validated in a UK sample.

#### Sociodemographic data

Pupil’s date of birth, gender, ethnicity, postcode and free school meal eligibility are obtained from school records.

#### Academic attainment

Academic attainment of participants is reported by their teachers. Staff rate participants’ attainment in mathematics, writing and reading on a five point scale. The scale ranges from ‘below expected’ to ‘above expected’ and teachers are asked to rate them according to their Age Related Expectations.

#### School level data

Schools complete a questionnaire designed to explore their facilities, initiatives and general environment relating to food, physical activity and health. Questions relate to the school’s food policies and the promotion of healthy eating; the school’s physical activity policies and other healthy lifestyle initiatives and future plans. The questionnaire was adapted from a questionnaire used previously in the West Midlands ActiVe lifestyle and healthy Eating in School (WAVES) cluster randomised controlled trial [20]. Additional questions were also included to to enable assessment of the cost of the intervention and its implementation.

#### Process evaluation

Semi-structured interviews will be conducted with classroom staff and head teachers/deputy head teachers in participating schools. An estimated 30 interviews from 12 case study schools will be conducted, until saturation. A purposive sampling approach will be used, aiming to obtain a wide range of schools and staff’s views. School characteristics could include size of the school, OFSTED rating and level of deprivation. Participant characteristics may include socio-demographics, years of teaching experience and their job role. Qualitative data will be analysed using constant comparison methods. New data will be compared, initially to previous data and, as analysis progresses, to the properties of emerging categories.

The qualitative interviews will examine the barriers and facilitators to undertaking initiatives, such as The Daily Mile, aiming to improve health and wellbeing. How staff implemented The Daily Mile in intervention schools will be explored in addition to the long-term potential to include it in the school day. Perceived challenges and factors facilitating the initiative will also be addressed. For the purpose of the economic evaluation, further questions will investigate the opportunity costs of The Daily Mile and the appropriateness of the outcome measures used to demonstrate effectiveness in this setting.

### Justification of sample size

The sample size calculation was based on the primary outcome (BMI z-score) and allowed for the clustered nature of the trial and that the primary analysis would adjust for baseline value of BMI z-score. A follow-up sample of 2000 participants across 40 schools (50 participants per school) gives the study greater than 90% power to detect a 0.125 difference in BMI z-score between the Daily Mile and comparator arms – which is a difference used in previous childhood obesity prevent trials [20]. Based on unpublished data from other studies, we expect that the mean (SD) BMI z-score in the control arm will be 0.35 (1.3). The trial is powered with an intracluster correlation coefficient (ICC) of 0.04, and a correlation between baseline and follow-up observations of 0.9. However, the study is robust to any changes in these correlations, and will have greater than 90% power for values of the ICC between 0.001 and 0.07, and have greater than 80% power for values of the ICC between 0.07 and 0.10. The trial is also robust to changes in the correlation between baseline and follow-up observations, and will have greater than 80% power for values greater than 0.8. A 20% dropout rate would still provide greater than 80% power to detect the pre-specified difference in means. No allowance has been made for any variation in cluster sizes as this is expected to be minimal. The sample size calculation was conducted using the clustersampsi function in Stata [21].

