### Planned statistical analysis

All statistical analysis will be conducted once the final set of measures (second follow-up) has been completed. Analyses will be by intention to treat and statistical significance will be considered at the 5% level (with 95% CIs reported). School and pupil level baseline characteristics will be presented by arm using appropriate summary measures (totals, percentages, means and standard deviations, medians and inter-quartile ranges). Characteristics will include age, ethnicity, deprivation, BMI z-score, physical fitness and wellbeing for individual participants. For schools; school size, ethnic mix and percentage eligible for free school meals will be reported.

As randomisation will be at the school (cluster) level, appropriate statistical methods to account for the clustering within schools will be used in the analysis. Analysis of outcomes will be for both 4 and 12-month follow-up measures. To evaluate effectiveness, a linear mixed model with follow-up outcome as the dependent variable and baseline values and treatment arm as the independent variables; with school included as a random effect. The primary analysis will also adjust for the variables used in the constrained randomisation (school size and proportion of pupils eligible for free school meals; and the average BMI Z-score of the school measured at baseline). We will allow for clustering at the school level and explore the possibility of allowing for an additional level of clustering at the year-group level. Secondary analysis will adjust for pre-specified pupil level factors which will include age, gender, baseline BMI z-score, ethnicity and deprivation from home postcode.

Outcome variables will be adjusted for the baseline values for the primary analysis. In addition, secondary analysis will adjust for pre-specified baseline school and child level covariates. These will include school level factors which were used in the randomisation (school size, average BMI z-score and % pupils eligible for free school meals) and pupil level factors (age, sex, baseline BMI z-score, ethnicity and deprivation from home postcode).

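### The stated power of over 90%, and the robustness claims built on it, do not follow from the protocol's own inputs: 40 schools of 50 pupils give about 82% power, and 53–65% at the edges of the ICC and correlation ranges called safe

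*Protocol article*

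**What the plan says.** The section Justification of sample size plans a follow-up sample of 2000 pupils in 40 schools, 50 per school. It states that this "gives the study greater than 90% power to detect a 0.125 difference in BMI z-score between the Daily Mile and comparator arms". The inputs are an SD of 1.3, an ICC of 0.04 and a baseline-to-follow-up correlation of 0.9, with nothing added for unequal cluster sizes.

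It then describes the design as robust to these correlations and makes four claims:

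- ICC, lower range: the study "will have greater than 90% power for values of the ICC between 0.001 and 0.07".
- ICC, upper range: it will "have greater than 80% power for values of the ICC between 0.07 and 0.10".
- Baseline correlation: it "will have greater than 80% power for values greater than 0.8".
- Dropout: "A 20% dropout rate would still provide greater than 80% power to detect the pre-specified difference in means".

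The section Study setting and participant eligibility confirms that 40 schools and about 2000 children are totals for the trial, not numbers per arm. The section Planned statistical analysis sets the 5% significance level with 95% confidence intervals.

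**The concern.** The section prints both a full set of inputs and the power they are said to give, so the one can be checked against the other. With 50 pupils per school, an ICC of 0.04 nearly triples the variance. Even with the large gain from baseline adjustment, 20 schools per arm looked too few for 90% power at a difference of 0.125. The claim that power stays above 80% at an ICC of 0.10, where the variance is inflated almost sixfold, looked less plausible still.

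This calculation concerns the primary outcome. A reader told that the type II error is below 10% and insensitive to the ICC and the correlation would give a null result more weight than the design supports. The Discussion lists the large sample as a strength and expects the results to influence policy.

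**Working it through.** **Inputs**

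| Input | Value | Source |
|---|---|---|
| Schools | 40 in total; k = 20 per arm | Sample-size section. No allocation ratio is stated; an equal split is assumed, which is the most favourable for power |
| Pupils per school, m | 50 | Sample-size section |
| SD | 1.3 | Sample-size section |
| ICC | 0.04 | Sample-size section |
| Correlation, r | 0.9 | Sample-size section |
| Difference | 0.125 | Sample-size section |
| Test | 5%, taken as two-sided because 95% CIs are reported | Planned statistical analysis |

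**Base case**

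- Design effect = 1 + (m − 1) × ICC = 1 + 49 × 0.04 = 2.96
- Variance factor for baseline adjustment = 1 − r² = 1 − 0.81 = 0.19
- Variance of the difference = 2 × 1.3² × 0.19 × 2.96 / 1000 = 0.001901, so SE = 0.0436
- 0.125 / 0.0436 = 2.867
- Power = Φ(2.867 − 1.96) = 81.8%. With a non-central t on 38 df it is 79.8%.

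The stated figure of more than 90% is not reproduced. A one-sided 5% test would still give only 88.9%.

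**Robustness claims, same formula with one input changed**

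| Case | Changed quantity | Power, normal (t) | Claimed |
|---|---|---|---|
| ICC 0.001 | design effect 1.049 | 99.8% (99.7%) | >90% |
| ICC 0.07 | design effect 4.43 | 64.9% (62.7%) | >90% |
| ICC 0.10 | design effect 5.90 | 52.8% (50.8%) | >80% |
| r = 0.8 | variance factor 0.36 | 54.9% (52.8%) | >80% |
| 20% of pupils lost | m = 40, design effect 2.56 | 78.7% (76.6%) | >80% |
| 20% of schools lost | k = 16 | 72.7% (69.9%) | >80% |

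**Where the thresholds lie (normal approximation)**

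- Power exceeds 90% only for an ICC up to about 0.027.
- Power exceeds 80% only for an ICC up to about 0.043, barely above the assumed 0.04.
- At ICC 0.04, 80% power needs r of at least about 0.895, and 90% needs about 0.923.
- The difference detectable with 90% power is 0.141 (0.145 with t).
- 90% power for 0.125 needs 432 pupils per arm before clustering; 432 × 2.96 / 50 = 25.6, so 26 schools per arm or 52 in total.

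**Other readings tried**

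| Reading | Base | ICC 0.07 | ICC 0.10 | r = 0.8 |
|---|---|---|---|---|
| Claimed | >90% | >90% | >80% | >80% |
| 40 schools per arm | 98.2% | 91.2% | 81.9% | 83.8% |
| Factor 1 − r in place of 1 − r² | 97.7% | 89.8% | 79.9% | 79.8% |
| SD of 1 | 96.1% | 86.1% | 75.2% | 77.3% |
| Change-score variance, 2(1 − r) | 79.8% | 62.7% | 50.8% | 50.6% |

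Only 40 schools per arm meets every claim, with the three edge values falling just above 90%, 80% and 80%. It also meets the dropout claim: 97.4% if pupils are lost, 95.2% if schools are lost. It contradicts the stated totals.

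**The case against.** The strongest reply is that the single correlation of 0.9 may apply only to pupils, with school means more strongly correlated over time. Write r_p for the pupil-level correlation and r_s for the school-level one. The effective correlation is then r = [m × ICC × r_s + (1 − ICC) × r_p] / design effect. With r_p = 0.9, r_s = 0.965 and 20 schools per arm, power is about 97% at base, 91% at ICC 0.07, 85% at ICC 0.10, 86% with r_p = 0.8, and 94% with 40 pupils per school. Every claim would then hold, and power would still fall as the ICC rises. The idea is not far-fetched, because the primary analysis also adjusts for the school's mean baseline BMI z-score.

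What stands of this is that the true power depends on a quantity the protocol does not give, so the recomputed values are what its stated assumptions imply, not a measurement of the trial's actual power. It does not rescue the text. Only one correlation is stated, and the result is sensitive to the second: with r_s = 0.95, power is 84.7% at ICC 0.07 and 75.4% at ICC 0.10, and those claims fail again.

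Three smaller points are fair. The claim of more than 90% power does hold at the low end of the ICC range, up to about 0.027. The dropout shortfall is slight (78.7% against 80%) if only pupils are lost. And the per-arm explanation cannot be proved from the document: the 1 − r variant misses the three edge thresholds by only 0.1 to 0.2 percentage points, and 95–97% power after dropout would be an odd thing to report as merely above 80%.

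**Conclusion.** The concern holds. Under the inputs as printed, power for a difference of 0.125 is 80–82%, not above 90%, so the type II error is about 18–20%. At ICC 0.07 and 0.10, inside the range presented as safe, the type II error is about 35% and 47%. At the three ICC and correlation limits the claims are out by 25 to 27 percentage points, too much for rounding or the choice between normal and t.

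This rests on equal allocation, a two-sided test, equal cluster sizes and one correlation acting at both school and pupil level. Unequal allocation or cluster sizes would lower power further; a school-level correlation well above 0.9 would raise it. That the total number of schools was entered as the number per arm remains an inference, and the finding does not depend on it.

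**What to change.** Keep the 40 schools and restate the sample-size section with 20 schools per arm:

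- Give the power as about 80–82% for 0.125, and the difference detectable with 90% power as about 0.14.
- Replace the robustness figures with about 65% at ICC 0.07, 53% at ICC 0.10, 55% at correlation 0.8, and 77–79% with 20% of pupils lost (70–73% if whole schools are lost).
- Delete the statement that the study is robust to changes in these correlations.

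If a different input was intended, such as a separate school-level correlation, state it, say at which level the 0.9 applies, and show that the printed figures follow from it.

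The cost is a text correction. The stated power becomes less favourable; recruitment, data collection and the analysis model are unchanged.

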### Study setting and participant eligibility

All Birmingham, UK schools with at least 20 pupils in school years 3 (aged 7–8 years) and 5 (aged 9–10 years) were eligible for participation in the Birmingham Daily Mile study. Initially eligible schools from an ethnically and socio-economically diverse part of the city (Northfield) were invited to participate and schools that expressed an interest in the trial were enrolled. Subsequent pragmatic invitation of eligible schools from a wider area was used to reach the recruitment target of 40 schools whilst ensuring the final sample included schools that varied in terms of ethnic make-up and levels of deprivation. The recruitment of forty schools will provide a sample of approximately 2000 children at follow-up.

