#### Recruitment of study participants

Pupils from one class in years 3 and 5 at participating schools were invited to take part in study measurements. Parents or caregivers received a letter describing the study and measurements it involved. If they agreed for their child to participate they provided consent by returning a signed consent form (Additional file 1). In addition, children were required to verbally assent to participating at the time of measurement. All children in schools allocated to the intervention arm will take part in The Daily Mile intervention. However, data collection is confined to those consented for study measurements.

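### The power statement assumes 50 pupils in every school, although eligibility and opt-in consent make school sizes vary; at about 82% recomputed power, that variation can bring power to or below 80%

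*Protocol article*

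**What the plan says.** All references are to the Methods of the protocol article.

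- **Justification of sample size** gives the main claim: "A follow-up sample of 2000 participants across 40 schools (50 participants per school) gives the study greater than 90% power". The target is a between-arm difference of 0.125 in BMI z-score, and the control-arm SD is put at 1.3. On correlations it says "The trial is powered with an intracluster correlation coefficient (ICC) of 0.04, and a correlation between baseline and follow-up observations of 0.9". It also promises more than 80% power after 20% dropout. On school size it says "No allowance has been made for any variation in cluster sizes as this is expected to be minimal".
- **Study setting and participant eligibility** sets the floor for a school: "All Birmingham, UK schools with at least 20 pupils in school years 3" (and year 5).
- **Recruitment of study participants** limits measurement to one class in each of the two year groups and makes it opt-in. Of parents it says: "If they agreed for their child to participate they provided consent by returning a signed consent form". The child must also assent at measurement.
- **Planned statistical analysis** specifies a linear mixed model with a random school effect and a 5% significance level.
- **Trial design and overview** says baseline measurement was done before schools were randomised.

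The article gives no CV of cluster size, no consent rate and no range of pupils per school.

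**The concern.** The expectation of minimal variation does not follow from the trial's own rules. If the floor of 20 is read per year group, a school at the floor can supply at most 40 pupils; read across both years, at most 20. The calculation assumes 50. Consent is opt-in, and schools were sought for their differences in ethnic mix and deprivation, so equal consent rates cannot be presumed.

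Variation in cluster size raises the variance of the treatment effect. If true power were well above 90%, a modest rise would not matter. It matters here because power recomputed from the stated inputs is close to 80% before any variation is allowed for. A null result would then be read against a power claim that the design does not deliver.

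**Working it through.** **Inputs.** From Justification of sample size: difference 0.125, SD 1.3, ICC 0.04, baseline correlation r = 0.9, 40 schools, m = 50. Assumed because the article does not state them: 1:1 allocation (k = 20 schools, 1000 pupils per arm) and a two-sided test at 5%. Also assumed: baseline adjustment multiplies the variance by 1 − r², with the ICC applied to what remains.

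**Step 1: the plan's own figure, equal clusters.**
- Adjusted variance = 1.3² × (1 − 0.9²) = 1.69 × 0.19 = 0.3211.
- Design effect DE = 1 + (50 − 1) × 0.04 = 2.96.
- SE = √(2 × 0.3211 × 2.96 / 1000) = 0.0436.
- Power = Φ(0.125/0.0436 − 1.96) = Φ(0.907) = **81.8%**. With a t reference on 38 df it is 79.8%.

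The stated figure above 90% is not reproduced. A one-sided test gives 88.9% and a change-score analysis 79.8%, so neither rescues it. Two other settings come near the published statements:

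| Setting | Base | ICC 0.07 | ICC 0.10 | r = 0.8 | 20% dropout |
|---|---|---|---|---|---|
| Stated | >90% | >90% up to here | >80% up to here | >80% above this | >80% |
| 20 schools per arm, 1 − r² | 81.8% | 64.9% | 52.8% | 54.9% | 78.7% |
| 40 schools per arm, 1 − r² | 98.2% | 91.2% | 81.9% | 83.8% | 97.4% |
| 20 schools per arm, 1 − r | 97.7% | 89.8% | 79.9% | 79.8% | 96.7% |

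Forty schools per arm satisfies every stated claim. A factor of 1 − r in place of 1 − r² comes close. The article does not show which, if either, was used.

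**Step 2: add variation in school size.** The CV is an assumed range.
- Simple design effect: DE = 1 + [(1 + CV²) × 50 − 1] × 0.04.
- Mixed-model efficiency: DE = 2.96 / [1 − CV² × L(1 − L)], where L = (50 × 0.04)/(50 × 0.04 + 0.96) = 0.676.

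| CV | DE, simple | Power, simple | DE, mixed model | Power, mixed model |
|---|---|---|---|---|
| 0 | 2.96 | 81.8% | 2.96 | 81.8% |
| 0.2 | 3.04 | 80.8% | 2.99 | 81.5% |
| 0.3 | 3.14 | 79.5% | 3.02 | 81.0% |
| 0.4 | 3.28 | 77.7% | 3.07 | 80.4% |
| 0.5 | 3.46 | 75.5% | 3.13 | 79.6% |

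Power crosses 80% at a CV of about 0.26 by the simple formula and about 0.45 by the mixed-model formula. With the t reference every entry is about 2 points lower, so all lie below 80%, including CV 0.

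**Step 3: 20% dropout (m = 40, 800 pupils per arm).**
- CV 0: DE = 1 + 39 × 0.04 = 2.56; power 78.7%.
- CV 0.3, simple: DE = 2.704; power 76.5%.
- CV 0.3, mixed model: L = 1.6/2.56 = 0.625, DE = 2.615; power 77.9%.

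The article states more than 80%.

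**The case against.** A reader might infer that unequal school sizes by themselves take power below 80%, or that they explain the shortfall from 90%. The documents support neither.

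- **No CV is given.** Falling below 80% under the normal approximation depends on an assumed CV. At 0.2 power stays above 80% by both formulas.
- **The simple design effect is pessimistic for this trial.** The planned mixed model weights schools more efficiently. At CV 0.3 the loss is then 0.8 points rather than 2.3.
- **One class per year group limits the spread.** Cluster size does not grow with school size. If classes held at most 30 (an assumption), no school could exceed 60. With a mean of 50, sizes between 40 and 60 cannot have a CV above 10/50 = 0.20. An extreme split per arm of 15 schools at 60 and 5 at 20 has CV 0.35. Summing n/[1 + (n − 1) × 0.04] over those schools gives an effective size of 324.7 against 337.8 for equal clusters, and power of 80.2%.
- **Most of the loss has another cause.** The fall from above 90% to 81.8% occurs at CV 0, as does the fall to 78.7% with dropout. If base power really were 98.2%, a CV of 0.5 would still leave 96.3% by the simple formula.
- **Baseline sizes are not follow-up sizes**, and schools are already recruited and randomised, so recalculation alters no design decision.

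All of this stands, and it makes the point secondary. It does not justify the sentence as written. The one-class rule caps the upper end only; it limits neither the lower end nor differences in consent. Nothing in the article supports the word minimal, and the recomputed margin above 80% is under 2 points.

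**Conclusion.** The point holds as a secondary correction to the power statement. Equal clusters of 50 are assumed without support, and the eligibility and consent rules make sizes vary. Power with equal clusters is about 82% (about 80% with t on 38 df), not above 90%, and that base error is the larger defect. At CV 0.3, variation in school size costs a further 0.8 points (mixed model) to 2.3 points (simple formula). It can bring power to or below 80%, but whether it does depends on a CV the article does not give. The claim of more than 80% power after 20% dropout fails even with equal clusters (78.7%), and falls to between 76.5% and 77.9% at CV 0.3.

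This rests on 20 schools per arm, a two-sided 5% test, a variance factor of 1 − r² with the stated ICC applied to the adjusted outcome, and the assumed CV range.

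**What to change.** Replace the sentence that makes no allowance for cluster-size variation with a recomputed power figure for 20 schools per arm. Use the mean and CV of consented pupils per school observed at baseline, with the expected dropout applied, because the figure of 50 refers to follow-up. Give the mixed-model efficiency result, which matches the planned analysis, alongside the simple design effect. Restate the claims of more than 90% power and of more than 80% after dropout to agree, and make this change together with the correction of the base calculation.

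Baseline was completed before randomisation, so the school sizes are in hand. The cost is one recalculation and a less favourable stated power; nothing in the conduct of the trial changes.
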